#### Secondary Outcomes

In addition to the anxiety-related part of the CINT questionnaire a Visual Analogue Scale-Anxiety - VAS-A [27] supported by the Faces Anxiety Scale [28] is used. Evaluation of potential discrepancies between the retrospectively reported anxiety and the measured anxiety during the ICU-stay is of particular interest. The State and Trait Anxiety Inventory - STAI [29] as a further anxiety-related instrument will be recorded to compare anxiety after ICU-stay.

Furthermore the CINT questionnaire [20,22] measures additional parameters of the ICU related experiences.

As a secondary variable, the patients' level of consciousness and concentration regarding a potential ICU-caused state of confusion will be surveyed with the Confusion Assessment Method for the ICU - CAM-ICU [25,26]. The test procedure CAM-ICU, also appropriate for ventilated patients, comprehends cognitive as well as process-related components. These components are illustrated using the Richmond Agitation and Sedation Scale - RASS [24] and the four delirium main criteria "acute onset", "inattention", "disorganized thinking" and "altered level of consciousness".

For the analysis of additional effects the duration of stays (ICU, intermediate care, standard ward, hospital) and routine date on the course of inpatient treatment are recorded. Socio-demographic data like age, gender, marital status and routine treatment data like medical diagnoses will be documented thoroughly.

Uncertainty tolerance will be measured using the Uncertainty Tolerance Scale [30] and semi-structured questions on convalescence are asked to get a qualitative impression of the participants health state.

Expected results will contribute to an improved communication in the ICU and finally to an improved quality of life as a desired treatment goal [31-33]. Therefore we will measure quality of life using the Schedule for Evaluation of Individual Quality of Life - SEIQoL [34], and the SF-12 [35]. For this reason we implemented a paper questionnaire version of the SEIQoL to test for acceptance of a self evaluation form for this kind of quality of life questionnaire.

All measurements and the timeline are summarized in Table 2.

**Table 2 T2:** Measurements.

t_0_	day of recruitment (ICU)	▪ Socio-demographic data, routine treatment data^2^ ▪ Acute ICU-Syndrome (CAM-ICU incl. RASS)^2^ ▪ Anxiety (VAS-A)^1^
t_1_	24 h after study intervention	▪ Acute ICU-Syndrome (CAM-ICU incl. RASS)^2^ ▪ Anxiety (VAS-A)^1^

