t_2_	48 h after study intervention	▪ Acute ICU-Syndrome (CAM-ICU incl. RASS)^2^ ▪ Anxiety (VAS-A)^1^

t_3_	admission to standard ward	▪ Experience and emotional state in the ICU (CINT-FB)^1^ ▪ Anxiety (VAS-A)^1^ ▪ State-Anxiety (STAI-State)^1^ Estimated time for the questionnaire: 20 minutes

t_4_	discharge from hospital	▪ In-patient history and postoperative complications^2^ ▪ Length of stay and mode of discharge^2^

t_5_	3 months after discharge (by mail)	▪ Individual quality of life (SEIQoL)^1^ ▪ Quality of life (SF - 12)^1^ ▪ Uncertainty (Uncertainty Tolerance Scale)^1^ ▪ Convalescence (Semi-structured questions)^1^ ▪ Trait-Anxiety (STAI-Trait)^1^ Estimated time for the questionnaire: 15 minutes

Points of measurement and outcome measures according to case report form.

^1^Self evaluation; ^2 ^Third-party evaluation

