### Drop-outs

Drop-outs will be documented thoroughly and included in the data analysis until the point of drop-out. Reasons for drop-out will be reported and analyzed.

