### Data analysis

Descriptive analyses will be carried out by standard methods, taking into consideration the scale of the respective variables. For analysis of the primary endpoint we will use an ANCOVA model with the primary endpoint as the response, and the center as a covariate, thus allowing for the stratified randomization procedure. The treatment effect will be reported as an adjusted difference in means with a corresponding 95% confidence interval. Secondary endpoints will be assessed with the respective adjusted models, using standard ANCOVA models for continuous outcomes and logistic regression for binary outcomes. In case of repeatedly measured outcomes, mixed models will be used for analyses to adjust for within-patient correlations [37]. Secondary endpoints analyses are considered as merely exploratory. The analysis of all outcomes will obey to the intention-to-treat principle. Subgroup analyses will be conducted as interaction tests, also in a non-confirmatory fashion [38].

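### Under the stated ANCOVA rule, a stay ended by death would count as a short stay; the durations of stay need a rule for deaths

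*Protocol article*

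**What the plan says.** Under Secondary Outcomes, the protocol article records, for additional effects, "the duration of stays (ICU, intermediate care, standard ward, hospital". In Table 2 the row for hospital discharge (t4) collects "Length of stay and mode of discharge".

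The Data analysis section gives one general rule for secondary endpoints, "using standard ANCOVA models for continuous outcomes", with logistic models for binary ones and mixed models where an outcome is measured repeatedly. It adds "The analysis of all outcomes will obey to the intention-to-treat principle". The Drop-outs section says that patients who drop out are "included in the data analysis until the point of drop-out". No analysis rule mentions death, and no time-to-event model, transformation or rank method is named. The same section limits the weight of these results: "Secondary endpoints analyses are considered as merely exploratory".

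**The concern.** A length of stay is continuous and is measured once per patient, so the general rule sends it to ANCOVA, which compares mean days. Intention to treat keeps patients who die in the comparison. A patient who dies on day 2 then contributes two days, exactly like a patient who leaves well on day 2. Short stay is read as good recovery, so deaths push the result in the favourable direction.

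The trial enrols unscheduled as well as scheduled ICU patients, so some in-hospital deaths are foreseeable. For intermediate-care and ward stay the difficulty is sharper: a patient who dies in the ICU has either a zero or no value, and the article does not say which. At stake is how an exploratory result on stay is interpreted. The anxiety endpoint is not involved.

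**Working it through.** **No figure to reproduce.** The article gives no mortality, no distribution of stay and no sample size for stay. Its one sample-size calculation concerns the primary endpoint. From it I use only the 100 patients per arm and the center split of 40/30/30 per arm. All other inputs below are assumptions, shown as a range.

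**1. Shift caused by deaths.** Let survivors have the same mean stay L_s in both arms, let stays ended by death average L_d, and let mortality be d0 and d1. The mean stay in an arm is (1 − d)·L_s + d·L_d, so the difference in means is −(d1 − d0)·(L_s − L_d).

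| L_s, L_d (days) | equal mortality | 5 points more deaths | 10 points more deaths |
|---|---|---|---|
| 14, 4 | 0 | −0.05 × 10 = −0.50 | −0.10 × 10 = −1.0 |
| 14, 7 | 0 | −0.05 × 7 = −0.35 | −0.10 × 7 = −0.7 |
| 10, 3 | 0 | −0.05 × 7 = −0.35 | −0.10 × 7 = −0.7 |

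The arm with more deaths appears 0.35 to 0.5 day faster for a 5-point gap (5% vs 10%, or 10% vs 15%) and 0.7 to 1.0 day faster for a 10-point gap (5% vs 15%).

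**2. Shift against noise.** For log-normal stay with mean m and log-SD s, the SD is m·√(exp(s²) − 1), and the standard error of the arm difference is SD·√(2/100). This ignores center adjustment and the mixing-in of deaths.

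- m = 10, s = 0.7: SD = 10 × 0.795 = 7.95; SE = 7.95 × 0.141 = 1.1 days.
- m = 14, s = 0.7: SD = 14 × 0.795 = 11.1; SE = 1.6 days.
- m = 10, s = 1.0: SD = 10 × 1.311 = 13.1; SE = 1.9 days.
- m = 14, s = 1.0: SD = 14 × 1.311 = 18.4; SE = 2.6 days.

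Set against this whole range, a 0.5-day shift is about 0.5/2.6 = 0.2 to 0.5/1.1 = 0.45 standard errors. Pairing each 5-point shift with its own mean narrows this to about 0.35/2.6 = 0.13 to 0.5/1.6 = 0.31.

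**3. Can such a gap arise by chance?** With 7.5% average mortality, the standard error of the difference in death proportions is √(2 × 0.075 × 0.925/100) = 0.037. A 5-point gap is 0.05/0.037, about 1.3 standard errors, so it needs no effect of the conversation on mortality.

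**4. Skewness.** ANCOVA with center was simulated on log-normal stays without deaths (4,000 runs, 100 per arm, stay multiplied by exp(−0.4 × log-SD) in one arm for the power columns).

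| log-SD | type I error, raw days | power, raw days | power, log days | power, rank test |
|---|---|---|---|---|
| 0.8 | 0.054 | 67% | 81% | 79% |
| 1.0 | 0.050 | 61% | 80% | 78% |
| 1.2 | 0.046 | 54% | 80% | 78% |

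Type I error holds. Power falls by about 13 to 26 percentage points against the log-scale analysis.

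**The case against.** The strongest reply is that the assignment is inferred. No sentence joins length of stay to ANCOVA, and the same paragraph under Secondary Outcomes also lists descriptors such as age and diagnoses. The Data analysis section lets descriptive methods follow the scale of each variable, so medians are not ruled out. The article is a condensed text, and an analysis plan that is not shown may deal with deaths. All of this stands, and it limits the weight of the point. It does not remove it: the article states a model for every continuous secondary endpoint without exception, and that model does not suit a stay that death can end.

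The second reply is that a conversation of about ten minutes, compared with another of the same length, gives no reason to expect a mortality effect. That also stands. A chance imbalance is noise over repeated trials rather than systematic bias. In the one trial that is run, though, the reported difference in days would still mix death with recovery.

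A reader might infer more than the documents support:

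- **That the effect on stay will have the wrong sign.** The documents contain no mortality or stay figures, and under plausible assumptions a 5-point gap moves the estimate by less than half a standard error.
- **That skewness makes ANCOVA invalid.** Type I error is preserved at this sample size. A difference in mean days is a legitimate target, and the log-scale analysis targets a ratio instead, so the power comparison is partly between different questions. That stays are skewed is itself an assumption.

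**Conclusion.** The point holds as a minor improvement. Read literally, the general ANCOVA rule and intention to treat together count an in-hospital death as a short stay, and no stated rule prevents it. The size depends wholly on assumed inputs: 0.35 to 0.5 day in favour of the arm with more deaths for a 5-point mortality gap, 0.7 to 1.0 day for a 10-point gap, and nothing when mortality and its timing are equal. The loss of precision from skewness is secondary. The confirmatory conclusion of the trial does not depend on any of this.

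**What to change.** Take the durations of stay out of the general ANCOVA rule:

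- **ICU and hospital stay:** analyse time to discharge alive with death as a competing event, showing cumulative incidence by arm and a cause-specific or Fine-Gray model adjusted for center. State which of the two models is used.
- **Reporting:** give deaths by arm next to every result on stay, with medians and quartiles.
- **Intermediate-care and ward stay:** report descriptively alongside deaths, because patients who die earlier never reach these units.
- **Scale scores (STAI, quality of life):** keep ANCOVA, and keep mixed models where a score is measured repeatedly.

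The change costs a few sentences and a standard analysis. It needs no new data, provided that the mode of discharge collected at t4 records death; the article does not say so, and the case report form should be checked. Sample size and primary analysis stay as they are. The downside is that the model yields a ratio rather than a difference in days, which the medians and cumulative incidence curves partly offset.

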### Protection of data privacy

We will create a pseudonym for all trial participants to collect and analyze the trial data. Key lists will be stored separately from the trial data and erased after final data analysis. Data will be analyzed in a way that no conclusions can be drawn to individual participants. Trial data is stored in lockable cabinets in lockable rooms.

### Quality assessment

The trial is part of the Nursing Research Network "Mitte-Süd". A report system is established within the network. Annual quality reports have to be prepared for the German Federal Ministry of Education and Research.

As the process of a multicenter trial demands high standards of quality to warrant comparable conditions and results among the centers all procedures were developed and documented in joint commissions.

### Publication policy

We plan to publish the trial results in a peer-reviewed, international, Medline-listed journal, independent of study results. This mainly serves the purpose to avoid publication bias. Additionally, we are obliged by the Federal Ministry of Education and Research to report our results within 6 months after study termination. All trial results will be reported within context to this study protocol.

### Ethical considerations

The study protocol is approved by the ethics committees of the universities in Marburg, Halle and Tübingen. If changes to the study procedures are necessary they will be proposed to the local ethics committees as amendments. All changes will be described and discussed in the publication of the trial's results.

## Discussion

In contrast to former trials on information programs on the ICU-stay our intervention will take place in the ICU. This approach will ensure to compensate for memory effects due to anesthesia or preoperative stress. Further the results will be applicable to non-elective ICU-patients. Thus our research will particularly contribute to the evidence on ICU-related information and communication.
